## Abstract

**Introduction:**

Pain is one of the most persistent symptoms after cancer treatment. The central nervous system can erroneously stay in its alarm phase, altering the pain experience of patients who have cancer. Pain neuroscience education (PNE) with multimodal approaches may benefit these patients.

**Objective:**

This protocol aims to determine the effectiveness of a PNE tool on pain, physical function and quality of life, as a supplement to a multimodal rehabilitation (MR) program in patients who had breast cancer (BC).

**Methods:**

An 8-week double-blinded randomized controlled trial will be conducted, including 72 participants who had BC and who have persistent pain, randomized into three groups: PNE program + MR program, traditional biomedical information + MR program and control group. The PNE program will include educational content that participants will learn through a mobile app and the MR program will include a concurrent exercise program and manual therapy. The primary outcome will be the perceived pain assessed using the Visual Analogue Scale and secondary outcomes are others related to pain, physical function and quality of life. All outcomes will be evaluated at baseline, at the end of the intervention and 6 months after the end of intervention.

**Discussion:**

The proposed study may help BC patients with persistent pain improve their pain experience, quality of life and provide for more adaptive pain-coping strategies. This protocol could propose an action guide to implement different integral approaches for the treatment of sequelae. This treatment option could be offered to this patient profile and it could be easily implemented in the healthcare systems due to its low costs.

**Trial registration:**

ClinicalTrials.gov, NCT04877860. (February18, 2022).

## Introduction

Despite the increasing incidence [1], more and more patients are surviving cancer due to developments in diagnosis and treatment [2]. However, survivorship does not mean to be illness-free. Persistent/chronic pain is defined as pain that persists for 3 months or longer [2]. Pain is one of the most frequent symptoms after cancer treatment. The burden of persistent pain can be overwhelming in breast cancer (BC) population which is already coping with a cancer diagnosis and treatment-related effects [3]. Moreover, incidence of persistent pain remains high, ranging between 11 to 57% in patients with BC [4].

The main therapeutic agents in cancer are chemotherapy, targeted therapy, immunotherapy, hormonal therapy, surgery, and radiotherapy. Chemotherapy may induce peripheral neuropathy causing neuropathic pain persisting for weeks or years post treatment [5]. Additionally, patients taking aromatase inhibitors to improve their overall survival are at risk of discontinuation during the first 12 months partly due to increased joint pain [6]. Up to 36% of survivors of BC taking aromatase inhibitors can suffer from arthralgia and joint pain [7]. Pain perceived by cancer survivors is often attributed to inflammation resulting from surgical procedures and radiation-induced fibrosis on affected tissues. In terms of shoulder function, a reduced range of motion and loss of strength related to persistent shoulder pain are common adverse effects in patients with BC [8].

Central sensitization (CS) as a new diagnosis label [9], is often accompanied by spreading pain, which extends outside the segmental area of primary nociception [10]. In some cases, after tissues have healed, the central nervous system (CNS) stays erroneously in its alarm phase [9]. This may be altering survivors’ of BC experience of pain, causing an increased responsiveness of nociceptive neurons in the CNS [10]. Apart from hyperalgesia, sensitivity can be altered to environmental stimuli such as weather, light, cold/heat, stress, food [11], and chemical stimuli (pesticides, odors) [12] in this CS context. Both peripheral and CS mechanisms have been identified in patients with BC [13].

Manual therapy may have immediate effect on cancer pain and may improve physical function [14]. Physical exercise enhances side effects derived from cancer treatment, such as fatigue, impaired physical function and pain [15]. Nevertheless, patients with persistent pain have more catastrophic thoughts and fewer adaptive coping strategies so might need a more biopsychosocial explanation of pain [16].

Educational interventions on pain management have mostly centered on traditional biomedical information (TBI), analgesics and explanations of perceived pain were based on tissue issues [17]. The recent paradigm shift in the conception of pain processing has led to pain neuroscience education (PNE) [18]. PNE consists of explaining the neurobiology and neurophysiology of pain and how pain is processed by the nervous system through the influence of stress, emotions, thoughts, sleep quality and various feelings. These biopsychosocial factors become even more important given that cancer patients must deal with a new body image, and possible sexual dysfunction [18]. Introducing PNE is important in cancer patients with persistent pain to decrease patients’ rumination about painful sensations and improve their perceived inability to control pain [19]. PNE in conjunction with other known physiotherapy interventions could ameliorate the prevention and treatment of pain related to medical treatment of cancer.

PNE has previously been used in the physiotherapy management of breast cancer patients with controversial results. Giving PNE instead of biomedical education can be more effective in reducing CS-related symptoms, pain catastrophizing, pain intensity, and pain interference [20]. However, the EduCan trial did not obtain better course of pain-related disability or pain intensity compared with biomedical pain education [21]. In addition, PNE and other physical recovery programs has no side effects [20, 22] and educational contents could be consulted on demand from any smartphone or tablet.

Some previous proposals have monitored and implemented therapeutic recommendations with mobile apps in health problems of high prevalence and high cost to our society, such as hip fractures [23] or the implementation of a recommendation system on energy balance (physical exercise and nutrition) [24] with promising success, both scientifically and socially.

The main aim is to study the short- and long-term effects of a PNE tool as a supplement to a multimodal rehabilitation (MR) program in BC patients with persistent pain upon finishing adjuvant treatment to determine its impact on pain, physical function and quality of life. Our hypothesis is that a PNE tool as a supplement to a MR program based on exercise and manual therapy techniques, will be more effective in improving persistent pain in cancer patients than an MR program combined with TBI. This will be compared to a control group.

## Methods

### Design

The protocol has been developed following the recommendations of the SPIRIT checklist. The study was approved by the Ethics Committee of the Junta de Andalucía (2205-N-20) in concordance with the Declaration of Helsinki. The PaiNEd trial was registered with ClinicalTrials.gov. ID: NCT04877860. A parallel three-arm superiority randomized controlled trial with assessors and data analyzers blinded to the interventions will be performed. Patients will be assessed at three different times, following the recommendations of the SPIRIT checklist and diagram (Fig 1): baseline (t_0_), at the end of the 8-week intervention (t_1_) and 6 months after the end of the intervention (t_2_). Assessments will be performed in 1 session of approximately 2 hours or two different sessions of 1 hour each.

**Fig 1 pone.0290096.g001:**
[figure not shown]
Schedule of enrollment, interventions and assessment following the SPIRIT diagram. AROM: Active range of motion; CS: Central sensitization; DNF: Deep neck flexor; MR: Multimodal rehabilitation; PNE: Pain neuroscience education; TBI: Traditional biomedical information.

Participants will be randomized into three arms (Fig 2). It will take about 2 years to collect and analyze all data. Participants will be recruited from the radiotherapy and oncology services of the "San Cecilio" University Hospital and the "Virgen de las Nieves" University Hospital, Granada, Spain. Interventions will take place at the CUIDATE unit (http://csaludable.ugr.es/pages/dossierultimo/%21), a cancer rehabilitation research unit of the Mixed University Sport and Health Institute, University of Granada.

**Fig 2 pone.0290096.g002:**
[figure not shown]
Overview of the study.

The inclusion and exclusion criteria for eligible participants of the study are detailed in Table 1.

**Table 1 pone.0290096.t001:** Inclusion/Exclusion criteria.

Inclusion criteria	Exclusion criteria
a) Survivors of BC cancer [25]	a) Physical or mental impossibility of carrying out the tests of the study
b) Aged 18 years or older	b) Have suffered chronic pain in the orofacial, cranial, cervical, brachial and shoulder areas or trauma to these regions prior to the cancer diagnosis
c) Have undergone surgery and/or have finished adjuvant treatment (radiotherapy and/or chemotherapy) at least 6 months up to 2 years ago	c)Participating in other physical recovery programs during the interventions
d) Have no active cancer	
d) Have pain ≥ 4 (VAS 0 to 10) in regions related to the tumor area (orofacial, cranial, cervical, brachial and shoulder) for more than 3 months. e) Pain can be compatible with one or more of these conditions: central sensitization, neuropathy, peripheral pain and pain from surgery	

BC = Breast cancer; VAS = Visual analogue scale.

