#### Multimodal rehabilitation program

The MR program features supervised exercise and manual therapy. It will be fully supervised by a physiotherapist who specializes in the implementation of exercise programs and manual therapy in the oncological population and will be individualized to the needs and circumstances of the participants.

*Exercise*. Patients will receive 3 nonconsecutive sessions per week at the CUIDATE unit, and the program will last 8 weeks. An overview of the exercise program is presented in Table 2. The combined resistance and aerobic exercise program will follow the American College of Sports Medicine (ACSM) exercise guidelines [29]. The first and third sessions of the week will consist of 60 minutes of concurrent exercise [30], and the second session will feature 60 minutes of aerobic exercise.

**Table 2 pone.0290096.t002:** Overview of the exercise program.

Principles		Concurrent exercise	
	Aerobic exercise		Resistance exercise
Frequency	3 sessions/week		2 sessions/week
Intensity	40–60% HRR		50–70% RM [32]
	Borg CR10 RPE: 3–4 [31]		Borg CR10 RPE: 5–7
Time	Session 1 of the week: 30 minutes		Session 1 of the week: 30 minutes
	Session 2 of the week: 60 minutes		Session 3 of the week: 30 minutes
	Session 3 of the week: 30 minutes		
Type	Elliptical cross-trainer exercise		Squats, stiff-legged deadlifts, shoulder press, unilateral rows, reversed flies and push-ups
			Week 1 to 5: 2x12-20 reps
			Week 6 to 8: 3x10-12 reps
Progression	40–50% HRR; Borg CR10 RPE: 3 (weeks 1 to 4)		When a participant can perform 2 sets, in 2 consecutive sessions with appropriate form, the exercise will be progressed through increasing the resistance by the smallest available increment
	50–60% HRR; Borg CR10 RPE: 4 (weeks 5 to 8) [33]		

HRR: Heart rate reserve; RM: Repetition maximum; RPE: Rating of perceived exertion

*Manual therapy*. Participants will receive 1 manual therapy session every 2 weeks. Each session will last approximately 30 minutes. Treatment sessions will be developed based on previously published protocols that demonstrate effectiveness in treating pain and dysfunction in oncology patients [33, 34]. The current protocol will involve manual and myofascial techniques focusing on the cranio-cervical, thorax and shoulder regions, adapted to the patient´s tissue response [35].

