*Active Range of Motion (AROM)*. A plastic universal goniometer with two adjustable overlapping arms is used to objectively measure the active range of motion of the shoulder joint with the patient placed in the supine position [49]. A cervical range of motion device (Performance Attainment Associates©, Spine Products, Roseville, MN, USA) is used to objectively measure the active range of motion of the cervical joints (sitting position and feet completely in contact with the floor) [50]. AROM measurements are bilaterally performed three times, and the average values are used for the study. Reliability of shoulder AROM was high in survivors of BC, with ICC values ranging from 0.66–0.97. [51]. Cervical AROM is reliable and valid for evaluating the cervical AROM (ICC range: 0.82–0.96) in patients with neck pain [52].

*Functional capacity*. The Six-Minute Walk Test (6MWT) determines the maximum distance (meters) that a person can walk in 6 minutes. The test take place in a 30-metre stretch of unimpeded walkway. Blood pressure, blood oxygen saturation and Borg’s modified Scale (0–10) of RPE are provided at the beginning and the end of the test. Heart rate is measured during the test. Patients are notified when each minute passes and standardized encouragement is given during the test [53]. The test has proven to be reliable as it obtained an ICC of 0.93 in cancer patients [54]. Minimal important difference was established between 22 m (95% CI 18–26) and 32 m (95% CI 20–42) [55].

*Hand-grip strength*. Grip strength is assessed with a manual dynamometer (TKK 5101 Grip-D; Takey, Tokyo, Japan) [56]. The test can be done with the patient in standing position. The elbow is fully extended, the forearm neutral for pronosupination and wrist extension between 0 and 30°. Patients are asked to squeeze the dynamometer as hard as possible. Phrases of encouragement are given to patients in order to achieve their maximum force. The test is repeated three times bilaterally to obtain the mean of each grip. ICC scores range from 0.88 to 0.96 demonstrating high reliability in survivors of HNC [57].

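### As written, Table 1 admits a breast cancer survivor with facial pain but not one whose only pain is in the breast, chest wall or axilla

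*Protocol article*

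**What the plan says.** Table 1 of the protocol article limits entry to adult survivors of breast cancer without active disease. Two inclusion items carry the letter (d); this point concerns the second. It asks for "Have pain ≥ 4 (VAS 0 to 10) in regions related to the tumor area" and then defines those regions in brackets. The full run is "in regions related to the tumor area (orofacial, cranial, cervical, brachial and shoulder) for more than 3 months".

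Item (e) states which kinds of pain are acceptable: "central sensitization, neuropathy, peripheral pain and pain from surgery". It names types of pain and adds no body region.

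Exclusion (b) uses the same five regions for pain that predates the cancer: "Have suffered chronic pain in the orofacial, cranial, cervical, brachial and shoulder areas or trauma to these regions prior to the cancer diagnosis".

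Under Multimodal rehabilitation program, the manual therapy consists of "manual and myofascial techniques focusing on the cranio-cervical, thorax and shoulder regions".

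The main aim, in the last paragraph of the Introduction, concerns breast cancer patients with persistent pain and sets no limit by body region. The Discussion draws its intended conclusions for the same broad group.

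**The concern.** In a breast cancer trial the tumour area is the breast and its surroundings. The list that is meant to define that area leaves out the breast, the chest wall and the axilla, but includes the face and the skull. The bracket therefore does not fit the phrase that it explains.

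What is at stake is who the trial represents. If the list is applied as written, the sample contains nobody whose pain is confined to the operated or irradiated site, although the objective and conclusions speak of persistent pain after breast cancer in general. If a recruiter lets the general phrase override the list, such patients are admitted, and eligibility then depends on the reading chosen. The comparison between the randomised arms is not biased by this, because the rule acts before allocation and equally on all three arms. The issue is the definition of the population and the reach of the conclusions.

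**Working it through.** No arithmetic applies. The sample-size inputs (15 mm, 90% power, 5% significance, 24 per group) do not enter the point, and the plan states no figure for the share of patients by pain site. The check sets the texts side by side.

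**Step 1: is the list closed?** The bracket contains five terms and no wording such as *for example* or *including*. No other inclusion item adds a region. Item (e) widens the type of pain only. Read literally, the list is closed.

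**Step 2: who qualifies?** Assume pain of at least 4 for more than 3 months and all other criteria met.

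| Site of pain | List read as closed | List read as examples of the general phrase |
|---|---|---|
| Breast, chest wall or axilla only | Does not qualify | Qualifies |
| Breast plus shoulder, arm or neck | Qualifies | Qualifies |
| Shoulder, arm or neck only | Qualifies | Qualifies |
| Face only | Qualifies | Qualifies (it is named) |

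The two readings differ only in the first row. The last row is the anomaly under either reading: facial pain counts as related to a breast tumour, and no reason is given.

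**Step 3: does the rest of the protocol share the restriction?**

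- *Main aim (Introduction):* persistent pain in breast cancer patients, with no regional limit. It does not match the list.
- *Rationale (Introduction):* survivors' pain is attributed in part to surgery and to fibrosis after radiation in the affected tissues. In breast cancer these include the breast and chest wall. It does not match.
- *Item (e):* accepts surgical pain, but under (d) only if it is felt in a listed region. For isolated pain at the surgical site the two items pull apart.
- *Manual therapy:* the thorax is treated, but pain there does not qualify. The cranio-cervical and shoulder regions do match.
- *Exclusion (b):* the same five regions as (d). The two criteria agree with each other, so any change to one has to be made in the other.

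**Step 4: size.** The group affected is the share of otherwise eligible survivors whose only pain of at least 4 is in the breast, chest wall or axilla. The document gives no distribution of pain sites, so this share cannot be stated.

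**The case against.** The strongest reply is that a focus on neck, shoulder and arm is a legitimate design choice that fits much of the protocol. The Introduction stresses shoulder pain with loss of motion and strength. The physical outcomes include shoulder and cervical range of motion, grip strength and deep neck flexor endurance. The Introduction also says that central sensitization can spread pain beyond the area where it began, which could explain remote regions such as the face and skull. Treating the thorax does not oblige the trial to recruit on thoracic pain. Axillary pain might in practice be recorded as shoulder or arm pain.

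Much of this stands, and it shows that a narrower target would be coherent. But the protocol never says that it has chosen one. It does not connect spreading pain with the region list, and it calls the listed regions related to the tumour area while leaving out the tumour site.

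Three stronger readings are tempting, and the document does not support them.

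- A reader might infer that pain at the tumour site is excluded. It is not. No exclusion names it, and a patient who has it together with qualifying shoulder, arm or neck pain can enter. The effect is failure to qualify when it is the only pain.
- A reader might infer from exclusion (b) that chest or breast pain predating the cancer will enter and dilute the effect. Such a patient enters only with separate qualifying pain in a listed region, and the document gives no basis for an effect on the result.
- A reader might infer that the list was carried over from a head and neck cancer protocol, since the grip-strength reliability is cited as "demonstrating high reliability in survivors of HNC" and the Data analysis section names cancer location as a covariate. That is a guess about origin. A reliability citation says nothing about eligibility, and the point does not need it.

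**Conclusion.** The point holds as a conflict between the eligibility rule and the stated question. Applied literally, the second item (d) admits facial pain and does not admit pain confined to the breast, chest wall or axilla. The general phrase in the same item, the unrestricted aim, item (e) and the treated regions do not share that restriction.

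The conclusion rests on reading the list as closed, which is its plain reading. If it was meant as examples, isolated breast pain would qualify, but the presence of orofacial and cranial would still need a reason. The size is unknown and limited to survivors with isolated pain at the tumour site. It would be too strong to say that the trial fails to enrol the pain it studies: shoulder and arm pain in breast cancer survivors falls within the aim. The correction should be made because the rule determines whom the result describes and is cheap to repair.

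**What to change.** Reconcile the region list in the second item (d) with the breast cancer population:

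1. Add breast, chest wall and axilla. Justify orofacial and cranial, or remove them.
2. Carry the same change into exclusion (b), so that the two lists stay identical.
3. Record the qualifying region or regions of each participant at t0, so that the report can show which pain was enrolled.

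If the present list is intended, keep it, give the reason, and restrict the objective and the conclusions to persistent pain in those regions.

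The cost is a short eligibility amendment, for which the Outcomes section already foresees a formal route with ethics approval, and one extra data item. The price of the wider list is a slightly broader mix of pain sites in the sample.

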### Randomization and blinding

Upon completion of the recruitment process, participants will be randomized (ratio 1:1) into each of the groups using a random number generation program (EPIDAT 4.2, Xunta de Galicia, Spain). Assessors and data analyzers will be blinded to the randomization of the participants. The blinding of assessors will be guaranteed by the fact that some members of the research group will perform first assessments and others will perform the post-treatment and follow-up assessments.

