#### Primary outcome (Perceived pain)

The visual analog scale (VAS), offers a subjective pain estimation. The VAS is a 100 mm straight line starting with 0 that represents “no pain” and ends with 100 representing “worst pain imaginable” [36]. The VAS has been used in multiple situations and has proven to be a reliable and appropriate tool to measure pain [36].

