*Deep Neck Flexor (DNF) endurance*. The DNF endurance test measures the endurance of the deep flexor muscles of the neck [58]. It consists of placing the patient in supine position with the spine fully supported on the stretcher and asking him to first, to do a flexion of the upper cervical spine and to simultaneously flex the lower cervical spine. The time that the patient is able to maintain the position without losing the initial distance that separated him from the stretcher is counted. The test will stop if the participant reports pain or if he can no longer maintain the position. Reliability of DNF endurance test was moderate as ICC = 0.66 [59].

*Body composition*. Direct Segmental Multi-frequency Bioelectrical Impedance Analysis (DSM-BIA) is used for assessing skeletal muscle mass (Kg), fat mass (%) and body weight (kg). DSM-BIA is evaluated using the In-Body 720 body composition analyzer (Biospace, Seoul, Korea), following the instructions of the user’s manual [60]. Patients will be told not to eat or drink one hour before the test. BIA appeared to have very high reliability at estimating body fat percentage in survivors of BC as ICC = 1 [61] and 0.95 at estimating muscle mass in women [62].

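### Changing the assessment team after baseline does not blind the later assessors and ties assessor team to time, and the double-blind label does not fit a trial whose participants know their treatment and rate the primary outcome.

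*Protocol article*

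**What the plan says.** The Randomization and blinding section makes a general claim, "Assessors and data analyzers will be blinded to the randomization of the participants", and then gives the mechanism: "The blinding of assessors will be guaranteed by the fact that some members of the research group will perform first assessments". For the visits after treatment a different set of people is used: "others will perform the post-treatment and follow-up assessments". The same section places randomization after recruitment: "Upon completion of the recruitment process, participants will be randomized (ratio 1:1) into each of the groups".

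The Design section names the same two blinded parties: "A parallel three-arm superiority randomized controlled trial with assessors and data analyzers blinded to the interventions will be performed". The abstract uses a wider label: "An 8-week double-blinded randomized controlled trial will be conducted". No section says that participants are blinded.

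The Intervention sections describe three visibly different packages: an education app plus supervised exercise and manual therapy, a leaflet plus the same rehabilitation, and the leaflet alone. The primary outcome is the VAS, which "offers a subjective pain estimation". The Data analysis section plans a 3x3 repeated-measures ANOVA with time as the within-subject factor and arm as the between-subjects factor.

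**The concern.** Three separate matters follow from these statements.

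- **The guarantee.** The assessors who need to be kept unaware of allocation are those who measure after treatment. Having someone else do the baseline hides nothing from them.
- **The rota.** With one team at baseline and another at both later visits, any systematic difference in how the teams measure is read as change over time. This matters where the examiner influences the result: goniometry, judging when the neck flexor position is lost, and encouragement during the walk and grip tests.
- **The label.** A reader of the abstract will assume that participants are blinded. They are not, and they supply the primary outcome. Assessor blinding cannot protect a self-rated pain score from expectation.

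At stake are the credibility of the blinding claim, the reading of within-arm improvements in the physical measures, and how far a VAS difference from the leaflet-only group can be attributed to treatment.

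**Working it through.** The article gives no figure for blinding, so there is nothing to reproduce. The check sets the statements side by side and then shows which contrasts the rota can reach.

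**Step 1: does the mechanism conceal allocation?** Randomization follows recruitment. If baseline precedes randomization, as that wording suggests, the baseline team has no allocation to learn. (The schedule figure is not shown, so the order cannot be confirmed.) Blinding then depends wholly on the later team. That team also belongs to the research group, and according to Data collection and security, participants come to the same unit for treatment and for assessment. The change of team does nothing to keep allocation from them.

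**Step 2: what does the rota confound?** Let the later team read *s* units higher than the baseline team, and let the true change in arm *g* be *δg*.

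- Observed change in arm *g*: *δg + s*. The time main effect carries the same *s*.
- Difference in change between arms *g* and *h*: (*δg + s*) − (*δh + s*) = *δg − δh*. The shift cancels.
- If the later team knows the allocation and shifts by arm, the difference becomes *δg − δh + (sg − sh)*, which does not cancel.

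**Step 3: illustration.** Only the 24 per arm comes from the article. The other inputs are assumptions, chosen to show the pattern and not to estimate any outcome: SD 16, correlation between visits 0.5, team shift 5 units, no true effect.

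- SD of a change: 16 × √(2 × (1 − 0.5)) = 16.
- Within-arm standard error: 16/√24 = 3.27, so the shift is 5/3.27 = 1.53 standard errors.
- Between-arm standard error: 16 × √(2/24) = 4.62, so a shift confined to the treated arms is 5/4.62 = 1.08 standard errors.

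Simulation of 4,000 trials, two-sided 5% tests, first arm and first arm against control:

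| Team shift | Mean within-arm change | Rejected | Mean between-arm difference | Rejected |
|---|---|---|---|---|
| None | 0.01 | 4.8% | −0.03 | 5.0% |
| 5 units, all arms | 5.10 | 31.8% | 0.11 | 4.3% |
| 5 units, treated arms only | 5.06 | 32.3% | 5.08 | 19.3% |

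The second row is the effect of the rota alone. The third row is what could follow if blinding of the later team failed.

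**Step 4: the label.** The abstract says double-blinded, while Design and Randomization and blinding name only assessors and analysts. A participant in the control group receives a leaflet and is invited to the programme after the measures are taken. A participant in either rehabilitation arm is scheduled for three exercise sessions a week for 8 weeks. The sample size is built on a 15 mm VAS difference from the control group, which is the comparison where participants' knowledge of their treatment is plainest.

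**The case against.** The strongest reply is that the article twice states that assessors and analysts are blinded. Operational safeguards, such as who holds the allocation list, are commonly left to the full protocol. That stands: their absence is not counted here, and the article does not show that blinding is absent. What remains is that it names one mechanism as the guarantee, and that mechanism cannot provide it.

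Second, the trial asks a between-arm question, and a common team shift cancels there. The VAS is self-rated, and the Outcomes section says questionnaires are collected through the app. This also stands. A reader might infer that the rota biases the primary comparison, or that a team offset would be reported as an effect on the article's Cohen's d bands. Neither is supported: the planned effect sizes are intergroup, so an offset common to all arms contributes nothing.

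Third, a reader might take the statement "Reliability of DNF endurance test was moderate as ICC = 0.66" and compute √(2 × (1 − 0.66)) = 0.82 outcome SDs as the noise caused by changing raters. The article does not say whether that coefficient is inter-rater, intra-rater or test-retest. The result is the total measurement error of a change, much of which could be present with a single rater. It is also the unfavourable end: the walk test's 0.93 gives √(2 × 0.07) = 0.37. No noise increment from the rota can be derived.

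Fourth, the Methods make clear who is blinded, and participants cannot be blinded to exercise against a leaflet. Both rehabilitation arms also receive the same programme and some form of education, so differing expectation is less obvious between them. This narrows the concern mainly to comparisons with control. It does not make the abstract's label accurate.

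**Conclusion.** The point holds in three limited parts.

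- The stated guarantee of assessor blinding does not follow from the change of team.
- Assessor team is aliased with baseline versus later visits. This reaches the time main effect and within-arm changes in assessor-measured secondary outcomes only. The group-by-time contrast is safe as long as the later team's shift does not depend on arm.
- The double-blind label conflicts with the article's own Methods. The primary outcome is rated by participants who know what they receive, most clearly those given only the leaflet. That participants are unblinded is inferred from the visibly different arms, since the article does not say so in words.

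No size can be given for expectation bias on the VAS. The size of any team difference is also unknown, so the 32% and 19% figures describe the assumed case only. None of this invalidates the primary between-arm analysis. The rota and the wording should be corrected, and comparisons with control should be read with the stated limit.

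**What to change.** Replace the blinding mechanism in Randomization and blinding. Draw assessors for all three visits from one existing pool, or at least balance assessors across arms. Balancing protects the between-arm contrast, but only a common pool also separates team from time. State that these assessors take no part in treatment or randomization and have no access to allocation, and that participants are asked not to disclose their arm.

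In the abstract, replace the double-blind description with: assessor- and analyst-blinded; participants not blinded; primary outcome participant-reported. State this as a limitation for comparisons with the control group.

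The cost is a constraint on the assessment rota and a less favourable blinding claim. Sample size and the planned model are unchanged.
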